### Recruitment of participants

2.4

Participants with insulin‐resistant type 2 diabetes mellitus are recruited from the outpatient clinics of the division of Endocrinology and Diabetology of the University Hospital Graz and form the Graz Diabetes Registry for Biomarker Research as well as via advertisement in local newspapers.

### Randomization

2.5

Participants are randomly assigned to one of the two groups, the intermittent fasting group or the control group in a 1:1 ratio. Randomization is performed using the randomizer tool ‘Randomizer for Clinical Trials’: http://www.randomizer.at/ (accessed 21 Oct 2019) from the Institute of Medical Informatics, Statistics and Documentation of the Medical University of Graz, Austria.

### Study hypothesis

2.6

We hypothesise that intermittent fasting over a period of 12 weeks can improve glycaemic control and body weight while being safe in people with type 2 diabetes and insulin therapy compared with usual care.

### Study outcomes

2.7

#### Primary outcomes

2.7.1

‐The impact of intermittent fasting on the glucose metabolism in participants with insulin‐treated type 2 diabetes mellitus assessed by the difference in the change of HbA1c from baseline to 12 weeks.‐The difference in the number of participants achieving a combined end point encompassing a body weight reduction of at least 2%, an insulin dose reduction of at least 10% and an absolute HbA1c reduction of at least 3 mmol/mol (0.3%).

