### Inclusion and exclusion criteria

2.2

The study population consists of participants with type 2 diabetes mellitus, aged between 18 and 75 years (both inclusive) and a glycated haemoglobin A1c of ≥7.0% (≥53 mmol/mol). Main inclusion criteria: total daily insulin dose ≥0.3 units per kilogram of body weight and stable bodyweight in the preceding 3 months (change in weight <±3 kg). Participants who are willing to comply with study procedures, attend the study site, participate in the necessary protocols and comply with fasting protocols are included in the study. Main exclusion criteria contain active, known malignancies within the last year (excluding intraepithelial neoplasia of prostate, gastrointestinal tract and basalioma), pregnancy or intention of becoming pregnant, breastfeeding, a history of any chronic disease process that could interfere with interpretation of study results, new hormonal supplementation or contraceptive hormonal medication changes in the last 2 months, type 1 diabetes mellitus or other forms of diabetes mellitus, an acute or chronic inflammatory disorder, alcohol abuse with more than 15 standard drinks per week, overnight shifts or intake of illicit substances.

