### Sample size estimation

2.3

Sample size was estimated using the parameters of a previously published randomized controlled trial^23^ that investigated the effects of intermittent fasting on glycaemic control in people with type 2 diabetes mellitus. We based our sample size estimation on the baseline HbA1c data of this study 66 ± 7 mmol/mol (8.2 ± 0.6%) and estimated that a sample size of 23 participants in each group will have a power of 85% to detect a clinically important mean difference of 6 ± 7 mmol/mol (0.5 ± 0.6%) in HbA1c between the groups at a two‐sided alpha error of 5%. For the co‐primary outcome a sample size of 20 participants in each group would provide a power of 0.80 to detect a difference in proportion of 40% between the intermittent fasting and the control group. This calculation assumes 10% of the control group will reach the co‐primary end point (combined end point encompassing a body weight reduction of at least 2%, an insulin dose reduction of at least 10% and an absolute HbA1c reduction of at least 3 mmol/mol [0.3%]).

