#### Justification of two primary outcomes

2.7.3

Lifestyle intervention trials in people with type 2 diabetes always face the problem that metabolic parameters, weight, and treatment can hardly be evaluated separately as they influence each other. For example, insulin dose decreases following weight loss will diminish the full impact of the weight loss on HbA1c reduction, while in contrast HbA1c reductions can simply be achieved by insulin dose increases without a contribution of the dietary intervention. Hence, as the parameters are interrelated, we believe that besides looking at the HbA1c change, it is also crucial to investigate a composite of weight, glycaemic control and insulin dose reduction. A weight loss of equal or more than 2% would indicate a weight change beyond the daily fluctuation.^24^ An insulin dose reduction of 10% or more is a pragmatic estimate and indicates better insulin sensitivity^25^ and an HbA1c reduction of at least 0.3% would be considered clinically meaningful.^26^

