#### Statistical assessment

2.8.19

We defined two primary outcomes for the study to capture both changes in glucose control and the change of glucose control in conjunction with the insulin dose and the body weight changes. We will analyse these two primary end points in a hierarchical order, where the difference in the change of HbA1c from baseline to week 12 between the study groups is analysed first (at a significance level of 0.05). If the null hypothesis of this primary outcome (i.e. there is no difference in the change of HbA1c from baseline to week 12 between the two study groups) is rejected, the second primary outcome (i.e. the difference in the number of participants achieving a combined end point encompassing a body weight reduction of at least 2%, an insulin dose reduction of at least 10% and an absolute HbA1c reduction of at least 3 mmol/mol [0.3%]) will be tested at a significance level of 0.05. As the analysis will be performed in hierarchical order, according to the European Medical Agency (EMA) guideline on multiplicity issues in clinical trials (section 5.1.2.) no reduction or splitting of the α level is required.^35^

For the primary analysis of the primary outcomes, we will perform an intention‐to‐treat (ITT) analysis of all participants randomized using an unpaired t‐test for the change in HbA1c (alpha = 5%), followed by a chi‐square test comparing the two proportions of the co‐primary outcome (alpha = 5%), if the first test rejects the null hypothesis.

We will then perform sensitivity analyses for the primary outcomes using multivariate imputation by chained equations) for missing data in the ITT cohort. Additional sensitivity analyses will be performed in the per protocol cohort (people adherent to the intervention according to section 2.8.19) without and with data imputation for missing data.

Furthermore, analysis of covariance or multiple linear regression model adjusting for baseline HbA1c and multiple logistic regression model adjusting for baseline co‐primary, respectively, will be performed using the ITT population.

Finally, we will perform linear mixed‐effect models without multiplicity adjustment and generalized linear mixed models, respectively, for the primary outcomes in the ITT population.

Continuous secondary outcomes will be analysed using both unpaired t‐test and linear mixed‐effect models.

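### The stated 85% power for the HbA1c outcome is not delivered by the printed inputs (about 81% or 79%); as a minor point, the responder cut-off is a rounded two-unit pair

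*Protocol article*

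**What the plan says.** Section 2.3 takes its planning values from the baseline HbA1c of an earlier randomised trial, printed as "66 ± 7 mmol/mol (8.2 ± 0.6" per cent. It sets the target at a "mean difference of 6 ± 7 mmol/mol (0.5 ± 0.6%) in HbA1c between the groups" and states that 23 per group give 85% power at a two-sided 5% level. Section 2.8.19 names an unpaired t-test on the change in HbA1c as the primary analysis. The second primary outcome is tested only if that test rejects.

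For the second primary outcome, section 2.3 gives 20 per group for "a power of 0.80 to detect a difference in proportion of 40" percentage points, with 10% responders assumed in the control group. The HbA1c criterion is "an absolute HbA1c reduction of at least 3 mmol/mol (0.3" per cent in section 2.7.1 and "an absolute HbA1c reduction of at least 3 mmol/mol [0.3" per cent in section 2.8.19. The Abstract and section 2.3 use the same pair. Section 2.7.3, which explains the choice, cites only the percentage: "an HbA1c reduction of at least 0.3% would be considered clinically meaningful".

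**The concern.** A power statement should be reproducible from the inputs printed beside it. Here the target difference and SD appear in two units, their ratios differ, and neither ratio gives 85% with 23 per group under the planned test. Because the testing is hierarchical, the power of the HbA1c comparison also limits the chance that the composite is tested at all. A reader who relies on 85% would overstate how informative a null HbA1c result is.

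The two-unit habit also touches the responder definition. An at-least rule classifies people at its exact value, so a rounded equivalent can classify someone near the boundary differently. The article does not say which unit decides.

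**Working it through.** **Inputs.** Difference and SD: 6 and 7 mmol/mol, or 0.5 and 0.6% (section 2.3). Group size 23, two-sided 5% (section 2.3). Test: unpaired t-test (section 2.8.19). The ± figure is taken as the within-group SD of the quantity compared, and all 23 per group are assumed to contribute.

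**Stated figure, HbA1c outcome.** Effect size d = difference/SD; noncentrality = d × √(n/2); degrees of freedom 2n − 2 = 44.

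| Pair | d | d × √(23/2) | Power, normal approximation | Power, t-test | n per group for 85%, t-test |
|---|---|---|---|---|---|
| 6 ± 7 mmol/mol | 0.857 | 2.907 | 0.828 | 0.811 | 25.4, so 26 |
| 0.5 ± 0.6% | 0.833 | 2.826 | 0.807 | 0.789 | 26.9, so 27 |

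The stated 85% is not reproduced. The normal approximation, n = 2(1.960 + 1.036)²/d², does not rescue it: it gives 24.4 and 25.9, so 25 and 26 per group.

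**What would reproduce it.** With 23 per group, 85% power needs d = 0.903. At a difference of 6 mmol/mol that is an SD of 6/0.903 = 6.64.

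**Stated figure, composite.** For 10% against 50% (mean 30%), the pooled-variance formula is n = [1.960√(2 × 0.3 × 0.7) + 0.842√(0.1 × 0.9 + 0.5 × 0.5)]²/0.4² = 19.4, so 20 per group, as stated. The two responder rates are assumed directly, so the unit of the HbA1c cut-off does not enter.

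**Cut-off in the two units.** The article's level pairs, "a glycated haemoglobin A1c of ≥7.0% (≥53 mmol/mol" and "66 ± 7 mmol/mol (8.2 ± 0.6", give (8.2 − 7.0)/(66 − 53) = 0.0923% per mmol/mol. Hence 3 mmol/mol = 0.277%, and 0.3% = 3.25 mmol/mol. The usual conversion line (% = 0.09148 × mmol/mol + 2.152, an assumption because the article does not print it) gives 0.274% and 3.28 mmol/mol.

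**Example.** With the assumed line, 60 mmol/mol is 7.64%, printed 7.6, and 57 mmol/mol is 7.37%, printed 7.4. The fall is 3 mmol/mol but only 0.2%. The article's own slope from 53 = 7.0% gives 7.65 and 7.37, so the same printed values.

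**How often.** With whole mmol/mol and one-decimal percentages on the assumed line:
- A fall of exactly 3 mmol/mol reads as 0.2% at 9 of the 38 whole baselines from 53 to 90.
- A fall of 2 never reads as 0.3%, and a fall of 4 always reads as at least 0.3%.
- Simulation with baseline 66 ± 7, an assumed change SD of 7 and mean falls of 0, 3 or 6 gives 1.3 to 2.2% of participants classified differently on this component. Times 46, that is 0.6 to 1.0 participants.

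**The case against.** **On power.** The best defence is rounding. The printed 6, 7, 0.5 and 0.6 are rounded, and an SD of 6.64 would print as 7, so unrounded inputs could have given 85%. This cannot be excluded, but those inputs are not printed. Rounding also works the other way: 5.5/7.5 mmol/mol would give 0.68, while 6.5/6.5 would give 0.91. The statement therefore cannot be verified as it stands, and the printed figures give less than it claims.

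**On the cut-off.** The defence largely stands. At the printed precision each figure is the other's conversion (0.277 rounds to 0.3; 3.25 rounds to 3). All four definitions put mmol/mol first, and section 2.7.3 gives a rationale, not a classification rule. Allowing for rounding in the two level pairs, the article's slope could lie between 0.079 and 0.108, which puts 3 mmol/mol anywhere from 0.24 to 0.32%. The pairs alone therefore do not prove a mismatch.

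**Stronger readings.** A reader might infer that two rival cut-offs leave the second primary outcome open to choice, with some 2 of 46 participants reclassified and the chi-square result at risk. The article does not support this.
- The figure of 2 of 46 (about 5%) requires converting whole mmol/mol changes to unrounded percentages and comparing them with 0.300. The article suggests no such step.
- It also ignores that a composite responder must meet the weight and insulin criteria too.
- Tables where one responder matters can be found (11 against 4 of 23, uncorrected p = 0.028; 10 against 4, p = 0.055). With continuity correction these become 0.059 and 0.109, and neither is significant.
- Near the planned 10% and 50%, 11 against 2 gives p = 0.003 and 10 against 2 gives 0.007, so one responder changes nothing.

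**Conclusion.** The point holds for the power statement. With 23 per group, the planned t-test has power of about 81% for 6 ± 7 mmol/mol and 79% for 0.5 ± 0.6%, so the stated 85% is 4 to 6 points too high for the inputs shown. This rests on the printed inputs, a two-sided 5% level and complete data.

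The shortfall is modest. It should not be blamed on the unit pairing, since both pairs fall short, nor read as a case for enlarging the trial: section 2.8.23 reports that all 46 participants have been recruited.

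The two-unit cut-off is a minor clarification. It affects about 1 of 46 participants or fewer on the HbA1c component and fewer on the composite, under the assumed conversion line and change SD. It does not affect the composite's sample size.

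**What to change.** In section 2.3, give the target difference and SD in one unit with the matching power: about 81% for 6 ± 7 mmol/mol, or about 79% for 0.5 ± 0.6%, with 23 per group. If the 85% came from unrounded inputs, print those inputs instead. Enrolment stays as it is.

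In the Abstract and sections 2.3, 2.7.1 and 2.8.19, state that the HbA1c criterion is judged on the laboratory mmol/mol value with a cut-off of 3, and mark the percentage as approximate. Use the same wording in section 2.7.3.

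The cost is a few words in each place, settled before the data are analysed, and a slightly less favourable power figure.

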#### Secondary outcomes

2.7.2

Differences in the change
in resting metabolic rate (RMR) from baseline to 12 weeksof glucose (area under the curve) within oral glucose tolerance test (oGTT) from baseline to 12 weeksin glycaemic pattern (continuous glucose monitoring [CGM]) from baseline to 12 weeksin body weight and body composition from baseline to 12 weeksin body composition (fat mass/lean body mass) from baseline to 12 weeksin mean 24 h blood pressure from baseline to 12 weeksin microbiome composition from baseline to 12 weeksin insulin dose from baseline to 4 weeksin insulin dose from baseline to 8 weeksin insulin dose from baseline to 12 weekson quality of life from baseline to 12 weeksin the sleep quality and sleep disturbances from baseline to 12 weeksin the sleepiness from baseline to 12 weeksin physical activity from baseline to 12 weeksDifferences in
time spent in hypoglycaemia, hyperglycaemia and number of hypoglycaemic events with symptoms and blood glucose <3 mmol/l (<54 mg/dl)number of severe hypoglycaemic events from baseline to 12 weeksof body weight after 64 weeksof HbA1c after 64 weeks

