The aim of the current study is to investigate safety and efficacy of intermittent fasting in people with type 2 diabetes mellitus and insulin therapy compared with usual care.

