#### Continuous glucose monitoring

2.8.5

Minimally invasive CGM measurement is performed using the Abbott FreeStyle Libre glucose monitoring device (Abbott Diabetes care). A sensor is introduced through the skin into the subcutaneous fat tissue. The upper arm is the main body location to applicate the sensors which are worn for 16 weeks (4 weeks insulin switch phase and 12 weeks intervention phase) by the participants. The Abbott sensor is factory calibrated and therefore does not require calibration by capillary prick blood. However, participants are instructed to scan the sensor with the corresponding recorder at least every 8 h. CGM data will be collected at on‐site visits.

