#### Insulin adaptation

2.8.18

To prevent hypoglycaemia caused by intermittent fasting,^23^ a specific protocol for insulin dose adaptation is used, adapted from Unnikrishnan et al.^34^ 4 weeks prior to the initiation of dietary intervention, participants switch to the same insulin treatment, consisting of glargine U300 as basal insulin and a short‐acting insulin. Insulin U300 is administered in the morning. Participants using premixed insulin receive 70% of their daily insulin dose as glargine U300 whereas participants using basal‐bolus insulin treatment continue on their original basal insulin dose but are switched to glargine U300. Participants who are allocated to the control group continue glargine U300 and prandial insulin as started in the switch phase with dose adjustments when deemed necessary by the treating physician.

Participants in the intermittent fasting group continue the same treatment as during the switch phase on the eating days and reduce the basal insulin by 20% on the fasting days with no prandial insulin. In case the blood sugar falls below 3.9 mmol/L, the fast is broken, and the glargine U300 dose is reduced by another 10% (on fasting and eating days) for the remainder of the study. (Table 1) Within the insulin switch phase, we standardise the insulin regimen but aim to sustain glucose control from screening without significant intensification of glucose control. During the intervention phase on days with 0% calorie restriction, we aim for 5.6–7.2 mmol/L in the fasting state and <11.1 mmol/L2h postprandial (for detailed insulin dose adjustments, see Table 2). Participants already using glargine U300 are able to start the intervention 7 days ±1 after the screening visit if treatment is stable at the discretion of the treating physician.

**TABLE 1 dme14813-tbl-0001:** Insulin regimen

	Eating days	Fasting days
Control group	Continue insulin dose from switch phase	Not applicable
Intermittent fasting group	Use insulin dose from switch phase	20% basal insulin reduction, no prandial insulin

**TABLE 2 dme14813-tbl-0002:** Insulin dose adjustment on fasting days and eating days

Fasting days	
<3.9 mmol/L	Fast stopped and additional 10% reduction of glargine U300 dose (on fasting and eating days), intake of 24 g of carbohydrates
3.9–5.5 mmol/L	Regular monitoring of glucose level trend
5.6–7.2 mmol/L	Target range
7.3–13.9 mmol/L	Regular monitoring of glucose level trend

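### The only count of non-severe hypoglycaemic events needs symptoms as well as glucose below 3 mmol/l, so no listed outcome shows how often low glucose occurred

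*Protocol article*

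**What the plan says.** Safety is one of the trial's questions. The Introduction states "The aim of the current study is to investigate safety and efficacy of intermittent fasting", and section 2.6 (Study hypothesis) expects the regimen to improve control and weight "while being safe in people with type 2 diabetes and insulin therapy compared with usual care".

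Section 2.7.2 (Secondary outcomes) lists four outcomes that bear on low glucose:

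- duration, within the item "time spent in hypoglycaemia, hyperglycaemia and number of hypoglycaemic events";
- the non-severe event count, the "number of hypoglycaemic events with symptoms and blood glucose <3 mmol/l (<54 mg/dl");
- a separate number of severe events;
- the change in CGM glycaemic pattern.

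Section 2.8.5 (Continuous glucose monitoring) says the sensors are "worn for 16 weeks (4 weeks insulin switch phase and 12 weeks intervention phase) by the participants" and that "participants are instructed to scan the sensor with the corresponding recorder at least every 8 h". Section 2.1 calls the trial open, and section 3 lists the unblinded CGM as a limitation.

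On fasting days section 2.8.18 (Insulin adaptation) acts at a higher level and without a symptom condition: "In case the blood sugar falls below 3.9 mmol/L, the fast is broken". Table 2 adds carbohydrate intake and a further basal insulin reduction.

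**The concern.** The expected hazard of fasting on insulin is low glucose, and much of it may go unnoticed. The one outcome that says how many non-severe episodes occurred keeps only those the participant felt. In an open trial, noticing and reporting symptoms can differ between arms for reasons unrelated to glucose. Sensor data do not depend on recall, and they are being collected through the whole intervention.

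The count also starts below the level at which the fasting-day rule intervenes. Few counted events in the fasting arm could mean that low glucose was rare. It could also mean that it was frequent but caught at 3.9 mmol/L by breaking the fast. The listed outcomes do not let a reader tell these apart, although the second would matter to anyone judging whether the regimen is safe and workable.

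**Working it through.** The plan gives no figure to reproduce here; the check is a comparison of definitions.

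**Units.** With 18.016 mg/dl per mmol/l:

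- 3 × 18.016 = 54.0 mg/dl, which agrees with section 2.7.2.
- 3.9 × 18.016 = 70.3 mg/dl.
- The event threshold lies 3.9 − 3.0 = 0.9 mmol/L (about 16 mg/dl) below the fasting-day action level.

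**Which listed outcome captures which episode.** The table reads the two conditions of the event count jointly. It assumes that time in hypoglycaemia is derived from the sensor with a threshold of at least 3.0 mmol/l.

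| Episode | Symptomatic event count | Time in hypoglycaemia |
|---|---|---|
| Below 3.0, noticed, day or night | counted | yes, as duration |
| Below 3.0, unnoticed, day or night | not counted | yes, as duration |
| 3.0 to below 3.9, with or without symptoms | not counted | open: no threshold stated |

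Severe events have their own count. The CGM pattern outcome is a change from baseline to 12 weeks and is not described as a number of episodes. The triggering of the fasting-day rule appears in no listed outcome.

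**Exposure to the rule.** Section 2.8 plans 3 fasting days a week for 12 weeks: 3 × 12 = 36 per participant. With 23 in the fasting arm, that is 23 × 36 = 828 planned fasting days. The listed outcomes do not show on how many of them the fast was broken for low glucose.

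**Comparability of the arms.** Table 1 marks fasting days as not applicable to the control group. Broken fasts therefore exist in one arm only and can be described but not compared. The randomised comparison is the episode count over all days, for which both arms have sensor data.

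**The case against.** The strongest reply is that hypoglycaemia is already measured in four ways. Time in hypoglycaemia has no symptom condition, so silent and night-time lows enter as duration; severe events are counted separately; the CGM pattern is also compared. Nothing says that safety will be judged on the symptomatic count alone. All of this stands. A reader might infer that the trial could declare the regimen safe on a measure blind to the relevant events, and the documents do not support that.

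Two other strong readings also fail:

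- Night-time events are not excluded. A symptomatic one below 3 mmol/l counts, and only unnoticed ones drop out.
- The 3.9 and 3 mmol/l levels do not contradict each other. One is a precautionary action level and the other an outcome level. An event prevented at 3.9 mmol/L did not occur, which is an effect of the regimen as delivered.

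It can also be said that an article leaves thresholds and breakdowns to the full protocol or analysis plan. That holds for the missing threshold of time in hypoglycaemia and for the split by type of day, and neither is a fault in itself. It does not cover the event definition, which the article does fix, with the symptom condition in it. Nor does duration stand in for frequency: one long episode and several short ones can give the same total time.

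**Conclusion.** The point holds as a cheap improvement to a secondary safety outcome. The only non-severe event count depends on self-report in an open trial and omits unnoticed episodes and all those from 3.0 to below 3.9 mmol/L. The other outcomes cover this partly, as duration or as the severe extreme. None shows how often low glucose occurred or how often the fasting-day rule was triggered.

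The number of missed episodes cannot be estimated, because the documents give no event rates. No primary outcome, test or sample size is affected.

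The conclusion rests on two assumptions. First, symptoms and glucose below 3 mmol/l are joint conditions; if two separate counts were meant, the outcome should say so. Second, the stored sensor record is complete enough to count episodes; it depends on participants scanning as instructed.

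**What to change.** Change the outcome definitions only; no clinical rule needs to change.

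1. From the stored CGM data, count episodes below 3.9 and below 3.0 mmol/L in both arms regardless of symptoms. Make this the between-group comparison over all days.
2. Keep symptomatic events below 3 mmol/l as a reported subset.
3. Apply the same two thresholds to time in hypoglycaemia.
4. In the fasting arm, report descriptively the number of fasts broken for low glucose and the split between fasting and eating days.
5. If outcome data have already been seen, label these analyses supplementary. Section 2.8.23 reports recruitment complete by 22 December 2021, so this should be checked.

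The cost is wording in the analysis plan and a count on data the trial already collects. Section 2.8.20 describes food diaries and two-weekly calls that could help identify broken fasts. The downside is higher reported counts, some of them sensor-artefact lows, so the report should say that the counts are sensor-based.

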**FIGURE 1 dme14813-fig-0001:**
[figure not shown]
Flow chart of the intervention (an optional single follow‐up after 1 year will be added)

46 participants (23 per group) with insulin‐treated type 2 diabetes mellitus are randomly assigned to ‘intermittent fasting’ or ‘control group’, in a 1:1 ratio. Intermittent fasting comprises 3 days (Monday, Wednesday, Friday) of 75% caloric restriction (i.e. only 25% of the recommended calorie intake; this intake is only allowed as breakfast and/or lunch to maintain an 18 hours period of fasting) and 4 days (Tuesday, Thursday, Saturday and Sunday) of 0% caloric restriction (i.e. ad libitum calorie intake) in 1 week.

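### The 64-week body weight and HbA1c outcomes are worded as levels, so the planned t-test would ignore baseline and lose precision, chiefly for weight

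*Protocol article*

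**What the plan says.** Section 2.7.2 (Secondary outcomes) of the protocol article holds two lists. The first is introduced as differences in change and includes body weight from baseline to 12 weeks. The second is introduced simply as differences, and it ends with "body weight after 64 weeksof HbA1c after 64 weeks". Section 2.7.1 defines the primary HbA1c outcome as a change from baseline to 12 weeks. Both variables are therefore changes at 12 weeks and, as printed, levels at 64 weeks.

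Section 2.8.19 (Statistical assessment) states: "Continuous secondary outcomes will be analysed using both unpaired t‐test and linear mixed‐effect models". Explicit baseline adjustment appears only for the primary outcomes, where the section names "analysis of covariance or multiple linear regression model adjusting for baseline HbA1c" and a logistic counterpart for the combined end point.

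The caption of Figure 1 describes the late visit as "an optional single follow‐up after 1 year will be added". No power or sample size is given for the 64-week outcomes.

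**The concern.** Body weight differs far more between people than a diet is likely to move it, and a person's later weight is closely tied to the starting weight. A comparison of raw kilograms at 64 weeks carries all of that between-person spread in its standard error. A comparison that uses the starting weight removes most of it. The baseline values are already needed for the 12-week outcomes.

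These are the only outcomes beyond 12 weeks, and section 3 names the short duration as a limitation. If the reported 64-week test is the t-test on levels, a sustained weight loss of moderate size would probably not be detected, and a wide interval could be taken as evidence that the effect had faded. The 12-week and 64-week results would also be on different scales, which makes persistence harder to read.

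**Working it through.** **Inputs from the article.** 23 per arm, two-sided 5% (section 2.3: "a sample size of 23 participants in each group will have a power of 85"% and a "two‐sided alpha error of 5"%). HbA1c: baseline SD 7 mmol/mol and target difference 6 mmol/mol (section 2.3). Weight loss of 3%-8% reported for intermittent fasting (section 4).

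**Assumed, not in the article.** Between-person weight SD *s* = 15-20 kg; correlation *r* between baseline and 64 weeks of 0.85-0.95 for weight and 0.3-0.7 for HbA1c; equal SD at both times; all 46 participants seen at 64 weeks. The 4 kg difference is illustrative; it is 4% at an assumed mean of 100 kg, within the 3%-8% range.

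**Formulas.**
- Level: SD = s
- Change score: SD = s·√(2(1 − r))
- Baseline-adjusted (ANCOVA): SD = s·√(1 − r²)
- SE of the difference = SD·√(2/23)
- Power from the noncentral t with 44 degrees of freedom

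**The plan's own figure first.** For HbA1c with difference 6 and SD 7, SE = 7 × √(2/23) = 2.06. Power at 23 per arm is 81% (t) or 83% (normal approximation), against the stated 85%; the normal approximation needs 25 per arm for 85%. On the percentage scale, an unrounded 0.55 with SD 0.6 gives 86% (t). The stated 23 is thus reproduced within rounding.

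**Body weight at 64 weeks, 4 kg difference.**

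| Assumed SD | r | SE level | SE adjusted | Power level | Power adjusted |
|---|---|---|---|---|---|
| 15 kg | 0.85 | 4.4 kg | 2.3 kg | 14% | 39% |
| 15 kg | 0.95 | 4.4 kg | 1.4 kg | 14% | 81% |
| 18 kg | 0.90 | 5.3 kg | 2.3 kg | 11% | 39% |
| 20 kg | 0.85 | 5.9 kg | 3.1 kg | 10% | 24% |
| 20 kg | 0.95 | 5.9 kg | 1.8 kg | 10% | 57% |

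Worked line: s = 18, r = 0.9 gives an adjusted SD of 18 × √(1 − 0.81) = 7.85 kg and an SE of 7.85 × √(2/23) = 2.31 kg.

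The variance ratio of level to adjusted is 1/(1 − r²): 3.6 at r = 0.85 and 10 at r = 0.95. The difference detectable with 80% power is 12.7-16.9 kg for levels and 4.0-8.9 kg with adjustment. For an 8 kg difference, the level test has 42% power at SD 15 and 26% at SD 20; adjusted at r = 0.9 these become 98% and 86%.

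**HbA1c at 64 weeks, difference 6, SD 7 mmol/mol.**

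| r (assumed) | Level | Change score | Adjusted |
|---|---|---|---|
| 0.3 | 81% | 67% | 85% |
| 0.5 | 81% | 81% | 91% |
| 0.7 | 81% | 96% | 98% |

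A change score has the smaller variance only when 2(1 − r) < 1, that is r > 0.5. At r = 0.5 adjustment removes r² = 25% of the variance.

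**The case against.** The strongest reply is that the t-test is only one of two stated analyses. A linear mixed model is planned as well. With repeated measurements per person it may well include the baseline value, and its terms are the kind of detail a journal article leaves to the full protocol or SAP. This stands: lack of baseline adjustment is shown for the t-test, not for the whole analysis of these outcomes, and the unstated model terms are not a fault in themselves. It does not remove the point, because the outcome itself is stated, and stated differently from its 12-week counterpart. The article also does not say which of the two analyses takes precedence.

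The list may also be loose shorthand, with change intended throughout; its grammar is uneven. That is possible, and it is a reason to state the definition, since the printed text puts the 64-week items under the stem without change.

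Three stronger readings are tempting and are not supported:
- **That between-person spread swamps any plausible effect on both outcomes.** For HbA1c the plan's SD of 7 is close to the target difference of 6, and the level test already has 81% power.
- **That the level comparison is biased by chance imbalance.** Under randomisation it is unbiased with a valid 5% error rate, and chance imbalance is already in its standard error. The loss is one of precision.
- **That the glucose-sensor outcomes in the same list, "time spent in hypoglycaemia, hyperglycaemia and number of hypoglycaemic events", share the defect.** The first list already has a baseline-referenced change in glycaemic pattern, and comparing hypoglycaemia between randomised arms is a legitimate safety comparison. Run-in length also varies: section 2.8.18 allows some participants to start about 7 days after screening instead of after a 4-week switch phase.

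**Conclusion.** The point holds in a limited form. As printed, the 64-week t-test for weight and HbA1c compares levels and makes no use of baseline; the mixed model may do so, but the article does not show it.

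For weight the cost is large under the assumed SD and correlation: about 10-14% power for 4 kg, against 24-81% with adjustment. The size depends on those assumptions, since the article gives no weight SD. For HbA1c the cost is modest, 81% against 91% at an assumed correlation of 0.5, and a simple change score would gain nothing at or below that correlation.

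Attrition at an optional visit would lower every figure; at 18 per arm, for example, the HbA1c level test falls to about 71%. The outcomes are secondary and have no part in the hierarchical test, so the primary conclusions are unaffected.

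**What to change.** In section 2.7.2, define both 64-week outcomes as the between-group difference in change from baseline to 64 weeks, in line with the 12-week outcomes.

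In section 2.8.19, replace the unadjusted t-test on levels for these two outcomes by ANCOVA with the baseline value as covariate, or by a mixed model that includes baseline and reports the week-64 contrast. Covariate adjustment matters more than the switch to change: with baseline as a linear covariate, the treatment estimate is the same whether the response is the 64-week value or the change, whereas an unadjusted change score could lose power for HbA1c.

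The cost is wording only. Baseline weight and HbA1c are already required, and no visits, measurements or participants are added. The wording should be settled before the 64-week data are analysed.
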